# Minimally invasive versus open distal pancreatectomy for pancreatic ductal adenocarcinoma (DIPLOMA): study protocol for a randomized controlled trial

**DOI:** 10.1186/s13063-021-05506-z

**Published:** 2021-09-09

**Keywords:** Minimally invasive, Laparoscopic, Robot-assisted, Distal pancreatectomy, Left pancreatectomy, Pancreatic tail resection, Pancreatic surgery, Pancreatic cancer, Pancreatic ductal adenocarcinoma

## Abstract

**Background:**

Recently, the first randomized trials comparing minimally invasive distal pancreatectomy (MIDP) with open distal pancreatectomy (ODP) for non-malignant and malignant disease showed a 2-day reduction in time to functional recovery after MIDP. However, for pancreatic ductal adenocarcinoma (PDAC), concerns have been raised regarding the oncologic safety (i.e., radical resection, lymph node retrieval, and survival) of MIDP, as compared to ODP. Therefore, a randomized controlled trial comparing MIDP and ODP in PDAC regarding oncological safety is warranted. We hypothesize that the microscopically radical resection (R0) rate is non-inferior for MIDP, as compared to ODP.

**Methods/design:**

DIPLOMA is an international randomized controlled, patient- and pathologist-blinded, non-inferiority trial performed in 38 pancreatic centers in Europe and the USA. A total of 258 patients with an indication for elective distal pancreatectomy with splenectomy because of proven or highly suspected PDAC of the pancreatic body or tail will be randomly allocated to MIDP (laparoscopic or robot-assisted) or ODP in a 1:1 ratio. The primary outcome is the microscopically radical resection margin (R0, distance tumor to pancreatic transection and posterior margin ≥ 1 mm), which is assessed using a standardized histopathology assessment protocol. The sample size is calculated with the following assumptions: 5% one-sided significance level (*α*), 80% power (1-*β*), expected R0 rate in the open group of 58%, expected R0 resection rate in the minimally invasive group of 67%, and a non-inferiority margin of 7%. Secondary outcomes include time to functional recovery, operative outcomes (e.g., blood loss, operative time, and conversion to open surgery), other histopathology findings (e.g., lymph node retrieval, perineural- and lymphovascular invasion), postoperative outcomes (e.g., clinically relevant complications, hospital stay, and administration of adjuvant treatment), time and site of disease recurrence, survival, quality of life, and costs. Follow-up will be performed at the outpatient clinic after 6, 12, 18, 24, and 36 months postoperatively.

**Discussion:**

The DIPLOMA trial is designed to investigate the non-inferiority of MIDP versus ODP regarding the microscopically radical resection rate of PDAC in an international setting.

**Trial registration:**

ISRCTN registry ISRCTN44897265. Prospectively registered on 16 April 2018.

## Background

Several randomized trials have suggested superiority of minimally invasive surgery over open surgery in terms of postoperative pain, morbidity, and length of hospital stay [1–5]. Minimally invasive distal pancreatectomy (MIDP), first described by Gagner in 1996 [6], is considered the standard approach for symptomatic benign and premalignant disease of the distal pancreas in many centers around the world [7, 8]. Although the number of pancreatic resections performed through a minimally invasive approach increased significantly during the past two decades, the initial introduction of minimally invasive pancreatic surgery has been rather slow [9, 10]. Recently, the first single- and multicenter, randomized, controlled trials comparing MIDP with open distal pancreatectomy (ODP) showed clear benefits of MIDP in terms of less intra-operative blood loss, a 2-day reduction in both time to functional recovery and length of hospital stay, and lower rates of delayed gastric emptying [5, 11]. However, these trials focused on MIDP for all indications (benign, premalignant, and malignant) and included only a minority of patients with pancreatic ductal adenocarcinoma (PDAC). Therefore, these trials were insufficient to draw any conclusions on the oncological outcome of the minimally invasive approach [5].

The oncological safety of MIDP remains a subject of debate which hampers its further implementation [12, 13]. A European survey on minimally invasive pancreatic surgery demonstrated that 73% (*n* = 148) of surgeons from 27 countries regularly performed MIDP [14]. Less than half of these surgeons, however, performed MIDP for PDAC and 31% expected MIDP to be inferior to ODP concerning oncological outcomes [14]. Consequently, many patients affected by PDAC might not receive MIDP due to uncertainty regarding oncological safety, and these patients do not benefit from the potential advantages. In theory, this enhanced recovery could potentially improve the use of adjuvant chemotherapy compared to ODP, as shown for other pancreatic resections [15–17].

Based on these results, the European Consortium on Minimally Invasive Pancreatic Surgery (E-MIPS) initiated the DIPLOMA study (distal pancreatectomy, minimally invasive or open, for malignancy). First, an international retrospective cohort study was performed including 1377 patients who underwent distal pancreatectomy (minimally invasive or open) for PDAC between 2007 and 2015 [18]. Patients after MIDP and ODP were matched using propensity scores in order to correct for standard demographics and known confounders. This study showed higher R0 resection rates for MIDP (67% versus 58%, *p* = 0.02), but lower median number of harvested lymph nodes [14 (interquartile range (IQR) 8–22) versus 22 (IQR 14–31), *p* < 0.001] with similar survival [29 (95% CI 23–35) versus 31 (95% CI 24–38) months for MIDP and ODP, respectively, *p* = 0.98] [18]. However, MIDP was associated with lower rates of lymphovascular tumor invasion, perineural tumor invasion, and lower lymph node stage insinuating that, despite matching, treatment allocation bias could still have influenced these results. Several other multicenter matched cohort studies on MIDP versus ODP for PDAC showed comparable outcomes, thus supporting the prevailing oncological uncertainty [19, 20].

The objective of the DIPLOMA trial is to compare the microscopically radical (R0) resection rate, survival, complications, quality of life, and costs after MIDP and ODP in patients with suspected or proven PDAC of the pancreatic body or tail. The outcome of the DIPLOMA trial will guide the further implementation of MIDP worldwide.

## Methods

### Design

The DIPLOMA trial is an international, randomized controlled, parallel-group, patient- and assessor (pathologist)-blinded non-inferiority trial comparing MIDP with ODP in patients with PDAC located in the pancreatic body or tail. Patients are randomly allocated to MIDP or ODP. Inclusion started after approval of the Medical Ethics Review Committee Board of Amsterdam UMC (location Academic Medical Center) in the Netherlands and the Research Ethics Committee of the University Hospital Southampton in the UK. Additionally, local approval was gained for every participating center. All patients provide a written informed consent before randomization. This protocol was developed according to the SPIRIT guidelines [21].

### Study population

Adult patients with an indication for elective distal pancreatectomy because of upfront resectable (proven or suspected) PDAC in the pancreatic body or tail are assessed for eligibility in the DIPLOMA trial (Figs. 1 and 2). PDAC is in this trial defined according to the WHO classification [22]. This may, albeit rare, also includes adeno-squamous carcinoma, colloid carcinoma (mucinous non-cystic carcinoma), hepatoid carcinoma, medullary carcinoma, signet ring cell carcinoma, undifferentiated carcinoma, and undifferentiated carcinoma with osteoclast-like giant cells.

**Fig. 1 Fig1:**
[figure not shown]
Study flowchart according to SPIRIT

**Fig. 2 Fig2:**
[figure not shown]
Schedule of enrolment, interventions, and assessments according to SPIRIT

### Inclusion criteria

In order to be eligible to participate in this study, a patient must meet all of the following criteria:
Age of at least 18 yearsElective indication for distal pancreatectomy for proven or suspected* PDACUpfront (without induction/down-sizing radiotherapy and/or chemotherapy) resectable PDAC in the pancreatic body or tail^#^The tumor is expected to be radically resected via both MIDP and ODP according to the local treating team^$^The patient is fit enough to undergo MIDP and ODP according to the operating team

*Pathological proof is not mandatory for two reasons. First, it is not common practice in PDAC of the pancreatic body or tail; the decision for minimally invasive or open surgery will therefore after the trial also depend on the “suspected” diagnosis. Second, there are some concerns regarding the safety of endoscopic fine needle aspiration of distal pancreatic cancers with the theoretical risk of peritoneal seeding.

^#^Neoadjuvant radiotherapy and chemotherapy are allowed only in case of an upfront resectable tumor. Induction treatment for an initially non-resectable tumor (i.e., locally advanced) is not allowed.

^$^Extended resections are allowed, with the exclusion of vascular resections, if according to the local treating team, feasible with both a minimally invasive and open approach. Extended resections, including adrenal gland resection, are defined according to the ISGPS guideline [23]. The preoperative CT scan of every randomized patient will be crosschecked by an expert panel, blinded for including center and treatment allocation.

### Exclusion criteria

Patients meeting any of the following criteria will be excluded from participation in this study:
American Society of Anesthesiology physical status above 3A medical history of chronic pancreatitis (according to the M-ANNHEIM criteria [24])Second malignancy necessitating resection during the same procedureDistant metastases (M1) including involved distant lymph nodesTumor involvement or abutment of major vessels (celiac trunk*, mesenteric artery, or porto-mesenteric vein)PregnancyParticipation in another study with interference of study outcomesMalignant transformed pancreatic cystic lesion

*The distance between the tumor and the celiac trunk has to be at least 5 mm.

### Randomization

Patient recruitment and the collection of written informed consent are performed at the outpatient clinic. Allocation of patients to MIDP or ODP is performed centrally by the study coordinators using a concealed online computer-controlled permuted-block randomization module (Castor EDC, CIWIT B.V., Amsterdam, the Netherlands). Randomization between MIDP and ODP will be performed in a 1:1 ratio. The block sizes will be subject to random variation with block sizes varying between 4, 6, and 8 patients. The entire randomization will be concealed to all involved investigators. Randomization will be stratified for annual distal pancreatectomy volume (< 20, 20–40, and > 40) of participating centers. In addition, randomization will be stratified for tumor involvement beyond the pancreas and spleen to correct for differences in extended resections (adrenal gland involvement is defined as extended resection according to the ISGPS guideline) [23]. Randomization will take place as soon as distal pancreatectomy is planned (i.e., date of surgery is available) in order to reduce the drop-out rate after randomization. Only patients that do not receive surgery are considered a drop-out and will not be analyzed. All other randomized patients (including patients with peroperative diagnosed metastasized disease) will be analyzed according to the intention-to-treat principle. Patients will be coded by a numeric randomization code and the study coordinator will be the only one with access to it. The source data will be stored digitally and will be kept by the project leader for 15 years after the last patient’s follow-up is completed.

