### Conversion from MIDP to ODP

Any incision used for other reasons than trocar placement or specimen extraction is defined as a conversion. Patients allocated to MIDP but converted to ODP will still be analyzed in the MIDP group, according to intention-to-treat principles. Reasons for conversion will be registered and categorized as urgent or non-urgent conversions [28].

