### Blinding

Within the DIPLOMA trial, all assessors of the primary outcome (i.e., the pathologists), the patients, and the adjudication committee are blinded for treatment allocation. Directly after skin closure, while still under general anesthesia, patients will receive a firmly taped, large 40 × 40 cm abdominal dressing to cover their incision(s) and therefore their treatment allocation (minimally invasive or open). This abdominal dressing will be removed when all criteria for functional recovery are met or earlier for medical reasons, such as suspicion of wound infection. If earlier inspection is required, attempts are made to maintain patient blinding. This blinding has proven to be successful in previous multicenter trials [5, 29, 30]. The success of blinding will be assessed using the blinding index as proposed by Bang et al. [31]. Both patients and pathologists will be asked about the alleged treatment allocation, based on five categories: (1) strongly believe it was MIDP, (2) somewhat believe it was MIDP, (3) somewhat believe it was ODP, (4) strongly believe it was ODP, and (5) do not know. Due to ethical and legal concerns, patient blinding will not be performed in participating centers from the USA and in patients who are intra-operatively diagnosed with irresectable disease, such as metastases. Since patient blinding only influences one of the secondary outcomes, time to functional recovery, and not the primary outcome, this is considered of minor influence. Sensitivity analysis, excluding centers from the USA and patients with perioperative diagnosed metastasized disease will be performed for analysis of time to functional recovery.

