### Secondary outcomes

The most important secondary outcomes are overall survival, time and site of disease recurrence, and postoperative time to functional recovery. Other secondary outcomes of this trial include intra-operative parameters (type of surgery (laparoscopic or robot-assisted), conversion, method of pancreatic transection, vessel resection, operative time, blood loss, and blood transfusion) and postoperative outcomes (major complications, delayed gastric emptying, pancreatic fistula, post-pancreatectomy hemorrhage, surgical site infection, serum levels of CA 19.9 and CEA, postoperative intervention, intensive care unit admission, organ failure, length of hospital stay, readmission, (time to) start of adjuvant therapy). Additional to the primary outcome, other pathology outcomes are recorded, such as tumor size, specimen length and weight, histology grading, distance from the tumor to all margins, number of retrieved lymph nodes, number of positive lymph nodes, lymphovascular and perineural tumor invasion, and venous and arterial tumor involvement. For the economical evaluation, costs (intra-operative and postoperative costs) and quality of life are assessed.

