### Data collection and patient follow-up

The required clinical data will be collected after randomization, i.e., from hospitalization up to 36 months postoperatively using standardized (online) case report forms (Castor EDC, CIWIT B.V., Amsterdam, the Netherlands) by the local treating physicians. All data is stored in an electronic database (Castor EDC, CIWIT B.V., Amsterdam, the Netherlands). Data monitoring is performed by the study coordinators who will crosscheck the case report forms with source data. Baseline characteristics (age, sex, performance status (Karnofsky score)), ASA physical status, body mass index, previous abdominal surgery, diabetes mellitus, preoperative imaging conclusion including tumor size and involvement of other organs and vessels, neoadjuvant treatment, serum levels of Hba1C, CA 19.9 and CEA, and baseline quality of life measures will be recorded before randomization. For all patients, the most recent preoperative imaging will be sent anonymously to the study coordinator. This will follow local ethical and privacy rules in every center. After completion of the study, all imaging modalities will be reassessed by two expert radiologists independently in order to define the preoperative pancreatic cancer stages. In case of disagreement between the expert radiologists, a third expert radiologist will be invited and discussion will take place until consensus is reached. The required clinical data will be collected after randomization, i.e., from hospitalization up to 36 months postoperatively using standardized (online) case report forms by the local treating physicians, and will be crosschecked with source data by the study coordinators. For quality of life, the EQ-5D-5L, QLQ-C30, and PAN-26 questionnaires are used. These will be sent to the participating patients at baseline, 14, 30, 90, and 180 days after surgery. Patients will also receive a questionnaire at 90 days and 365 days after surgery which focuses on readmissions, complications, body image, and adjuvant therapy. Patients will be followed up at the outpatient clinic every 6 months during the first 2 years after surgery and after 36 months after surgery (i.e., at 6, 12, 18, 24, 36 months). During these follow-up moments, patients will undergo an abdominal CT scan and serum levels of CA 19.9 and CEA tumor markers will be assessed.

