### Statistical aspects

#### Sample size calculation

The DIPLOMA trial is designed as a non-inferiority trial, hypothesizing that in patients with pancreatic cancer the rate of microscopically radical (R0) resection rate of MIDP is non-inferior to ODP. Based on data collected for the retrospective DIPLOMA cohort study (1377 patients, matched based on propensity scores) [18], the sample size is calculated with the following assumptions: 5% one-sided significance level (*α*), 80% power (1-*β*), expected R0 rate in the open group of 58%, expected R0 resection rate in the minimally invasive group of 67%, and a non-inferiority margin of 7%. Based on these assumptions, a sample size of 226 patients (113 patients per arm) is required. Including 2.5% drop-out after randomization (patients who undergo no surgery after randomization) and 10% metastasized disease leads to a total number of patients to be randomized of 258 (129 per study arm).

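### Randomised patients who are not operated on are left out of every analysis, with no exemption for overall survival, which could be observed in all of them

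*Protocol article*

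**What the plan says.** The protocol article sets the exclusion in the Randomization section: "Only patients that do not receive surgery are considered a drop-out and will not be analyzed". The next sentence defines who remains: "All other randomized patients (including patients with peroperative diagnosed metastasized disease) will be analyzed according to the intention-to-treat principle". The section on conversion uses the same principle for patients who are converted; they "will still be analyzed in the MIDP group, according to intention-to-treat principles".

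Allocation comes before the operation: "Randomization will take place as soon as distal pancreatectomy is planned (i.e., date of surgery is available". The Blinding section says that "the pathologists), the patients, and the adjudication committee are blinded for treatment allocation"; surgeons are not on that list.

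The Sample size calculation budgets for the excluded group: "Including 2.5% drop-out after randomization (patients who undergo no surgery after randomization").

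On outcomes, the article states: "The most important secondary outcomes are overall survival, time and site of disease recurrence, and postoperative time to functional recovery". The Statistical analysis section gives overall survival no population of its own. Its best-case and worst-case sensitivity analysis is for patients lost to follow-up, and the only other analysis set it names is as treated. On follow-up, the article says: "The required clinical data will be collected after randomization, i.e., from hospitalization up to 36 months postoperatively".

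**The concern.** Whether a randomised patient reaches the operating theatre is decided after allocation. Removing patients on that basis gives up, for those patients, the protection that randomisation provides. If the decision not to operate were related to the arm, the two operated groups would no longer be comparable.

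For R0 the exclusion can be defended, because without an operation there is no specimen to assess. For overall survival it cannot be defended in the same way, since survival can be observed in every randomised patient whether or not surgery took place. The Discussion calls long-term survival the most relevant outcome for these patients and describes R0 as its surrogate. The survival comparison is therefore the one that most needs all randomised patients, and nothing in the document brings the excluded ones back.

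**Working it through.** **Inputs** (Sample size calculation, protocol article): one-sided alpha 0.05, power 0.80, R0 rate 58% open (ODP) and 67% minimally invasive (MIDP), margin m = 7 points, 113 per arm evaluable, 2.5% without surgery, 10% metastasised, 258 randomised (129 per arm).

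**1. Reproduce the plan's figures.**
- n per arm = (z0.95 + z0.80)² × [pO(1 − pO) + pM(1 − pM)] / (pM − pO + m)²
- = (1.645 + 0.842)² × (0.2436 + 0.2211) / 0.16² = 112.2, so 113 per arm and 226 in total. The restricted-null variance of Dunnett and Gent gives 112.5, also 113.
- Inflation: 226 / (1 − 0.125) = 258.3, or 226 / (0.975 × 0.90) = 257.5. Both agree with 258.

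The sample size is not in question.

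**2. Size of the excluded group.** 0.025 × 258 = 6.45, taken as 6 patients. All in one arm, that would be 6/129 = 4.65% of the arm.

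**3. Effect on R0 if the excluded patients are counted as not R0 in their allocated arm.** Assumptions: the planning rates hold in operated patients, and metastasised disease is ignored. Power = Φ[(pM − pO + 0.07)/SE − 1.645], with SE = √{[pM(1 − pM) + pO(1 − pO)]/129}.

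| Patients without surgery | MIDP | ODP | Difference (points) | Power |
|---|---|---|---|---|
| None | 67.0% | 58.0% | 9.0 | 84.6% |
| Even, 2.5% per arm | 65.325% | 56.55% | 8.8 | 83.2% |
| All 6 in MIDP (0.67 × 123/129) | 63.9% | 58.0% | 5.9 | 68.4% |
| All 6 in ODP (0.58 × 123/129) | 67.0% | 55.3% | 11.7 | 92.8% |

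The one-sided extremes shift the difference by 6/129 × 0.67 = 3.1 points or 6/129 × 0.58 = 2.7 points. That is about 39 to 45% of the 7-point margin.

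**4. How likely the extreme is.** If not being operated on is unrelated to arm, the probability that all 6 fall in the same arm is 2 × 0.5⁶ = 3.1%.

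**5. Dependence on the metastases assumption.** If the 10% with metastases are also counted as not R0, evenly by arm, the rates become 0.875 × 58% = 50.8% and 0.875 × 67% = 58.6%, and power at 129 per arm is 77.7%. How operated patients with metastases are counted for R0 therefore matters more than the 2.5%.

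**6. Overall survival.** The document gives no effect size or event count for survival, so no bias or power can be computed. All that can be said is that about 6 of 258 randomised patients would be missing from the survival curves.

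**The case against.** The strongest reply is that nothing is hidden. The exclusion is stated openly, intention-to-treat is claimed only for the other randomised patients, and the sample size allows for the loss. A reader might infer that the article contradicts itself by calling the analysis intention-to-treat. It does not: it describes a modified intention-to-treat set without using that name. This part of the reply stands, and the label is a matter of wording.

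The route to bias is also narrow:
- A surgeon who changes approach still operates, so that patient stays in the allocated arm.
- Patients are blinded outside the US centres, so withdrawal there should not follow knowledge of the arm.
- Randomisation is held back until a surgery date exists, expressly to limit drop-out.
- Eligible patients must be judged suitable for both approaches.
- Nothing suggests that progression or deterioration before surgery differs by arm.

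What remains is a decision by the treating team not to operate. The Randomization section says that the randomisation is concealed from investigators, but surgeons must learn the allocated approach in order to perform it, and the article does not say when they do.

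Two stronger readings of the size should be resisted. A reader might set 4.65% of an arm beside the 7-point margin and call it two thirds of the margin. That compares a share of patients with a risk difference; the R0 shift is 2.7 to 3.1 points. A reader might also suppose that the missing patients are mostly early deaths. The article gives neither the reasons for no surgery nor the outcome of such patients.

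Finally, the analysis plan still to be drafted could define a survival population. That is possible, but it would have to override a rule that the protocol already states without qualification.

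**Conclusion.** The point holds in a limited form. As written, the protocol removes all non-operated randomised patients from analysis, and nothing exempts overall survival. That survival is covered is read from the unqualified wording, since the rule does not name it. The expected loss is about 6 of 258 patients, if the planned 2.5% is right; that figure is an assumption and not a cap.

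With even losses the effect on R0 is negligible (9.0 to 8.8 points). In the unlikely extreme it is about 3 points in either direction, which is sizeable against a 7-point margin. The document does not show that bias will occur; it leaves open a possibility that is cheap to close. The sample size and the operated set as the primary R0 population can stand.

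**What to change.** 1. Analyse overall survival from the date of randomisation in all randomised patients, by allocated arm, as far as consent to follow-up allows.
2. Keep the operated set defined in the Randomization section, including patients with metastases found at surgery, for the primary R0 analysis, and call it modified intention-to-treat.
3. Add an R0 sensitivity analysis that counts non-operated patients as not R0 in their allocated arm.
4. Report the number of patients without surgery, and the reasons, by arm.

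The cost is small but not nil. Vital status must be obtained for about 6 patients whose follow-up is at present timed from hospitalisation or surgery. Some who withdrew may not permit it, and 217 of 258 patients had already been randomised when the article was submitted, so part of the collection would be retrospective. The analysis plan was still to be written before database lock, so the change can be made there.

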#### Statistical analysis

Primary and secondary endpoints will be crosschecked with data from primary sources, and a blinded adjudication committee will check them against the used definitions. The primary endpoint (R0 resection rate) will be tested for non-inferiority using the chi-square test as described by Dunnett and Gent [40]. The distribution of variables will be determined using several plots (boxplot, Q-Q plot, and histogram) and the Kolmogorov-Smirnov, Shapiro-Wilk, and Levene’s tests as appropriate. For comparison of normally distributed continuous variables, the independent samples *t*-test will be used and values will be expressed as means with standard deviations. Continuous non-normally distributed variables will be compared using the Mann-Whitney *U* test and values will be expressed as medians with interquartile ranges. Categorical variables will be compared by chi-square or Fisher’s exact test as appropriate, and values will be expressed as proportions. A two-tailed *p*-value < 0.05 will be considered statistically significant. Where possible, risk ratios with 95% confidence intervals will be reported. For the primary study outcome, the lower limit of the two-sided 90% confidence interval of the difference in proportions will be reported and compared with the non-inferiority margin. Time to event endpoints, such as time to functional recovery, time to recurrence, and overall survival, will be calculated using Kaplan-Meier estimations. A Cox regression analysis will be performed to investigate predictors of postoperative survival. All parameters with a *p*-value < 0.1 in a univariable analysis are included in the multivariable Cox regression analysis. Multivariable logistic regression analyses are performed to determine predictors for primary and secondary study outcomes, for example, R0 resection, the occurrence of major complications, and postoperative pancreatic fistula. Predictors for receiving adjuvant chemotherapy will be assessed and additional “as treated” analysis will be performed. Subgroup analysis will be performed comparing outcomes for patients with and without neoadjuvant chemotherapy. Intra-operative details and primary endpoint of this study are expected to be complete. For patients who are lost to follow-up, a sensitivity analysis will be performed to determine best case and worst case scenarios. A detailed statistical analysis plan will be drafted prior to database lock. Despite all prior preventive measures taken, a complex international trial may evoke unforeseen situations after database lock that threaten data integrity and can only be resolved by unlocking the database prior to the final analysis. For purpose of transparency and reproducibility, the statistical analysis plan will therefore also describe the procedure to be followed when such situations arise.

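### Patients found metastasised at surgery are kept in the analysis but left out of the sample-size basis, and have no R0 status

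*Protocol article*

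**What the plan says.** - **Protocol article, Randomization.** Only patients who have no operation count as drop-outs and leave the analysis. For the rest: "All other randomized patients (including patients with peroperative diagnosed metastasized disease) will be analyzed according to the intention-to-treat principle". No outcome is exempted.
- **Protocol article, Sample size calculation.** 226 patients (113 per arm) are required. This is raised for 2.5% who have no surgery, "and 10% metastasized disease leads to a total number of patients to be randomized of 258 (129 per study arm").
- **Protocol article, Primary outcome.** R0 is a margin-to-tumour distance of at least 1 mm at the transection and posterior margins, so it needs a resected specimen.
- **Protocol article, Blinding.** Metastases found during surgery are given as an example of irresectable disease.
- **Protocol article, Statistical analysis.** "Intra-operative details and primary endpoint of this study are expected to be complete". Best-case and worst-case analyses are planned, but only for patients lost to follow-up.

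**The concern.** The analysis rule and the sample-size basis treat the same patients in opposite ways. One keeps those found metastasised at surgery; the other discounts them in the same way as drop-outs. No section limits the R0 comparison to resected patients or says what R0 value an unresected patient receives.

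This is more than missing detail. A later analysis plan that restricts R0 to resected patients departs from the Randomization rule, and one that keeps everyone departs from the basis of the 258. The group is about a tenth of each arm and the margin is 7 points. The choice also decides what is estimated: the R0 rate given resection, or the rate of achieving an R0 resection among all operated patients. In a non-inferiority trial, adding patients with the same result to both arms pulls the difference towards zero.

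**Working it through.** **Inputs.** From Sample size calculation: "5% one-sided significance level", 80% power, "expected R0 rate in the open group of 58" per cent, "expected R0 resection rate in the minimally invasive group of 67" per cent, and "a non-inferiority margin of 7" per cent. From Randomization: "Randomization between MIDP and ODP will be performed in a 1:1 ratio". The 2.5% and 10% allowances are the protocol's. Two things are assumed where marked: 10% metastasised in each arm, and unresected patients counted as not R0.

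**1. The plan's own figures.**
- n per arm = (1.6449 + 0.8416)² × (0.67×0.33 + 0.58×0.42) / (0.09 + 0.07)² = 6.183 × 0.4647 / 0.0256 = 112.2, so 113 per arm and 226 in total. Power at 113 per arm is 80.2%.
- Both allowances: 226 / (0.975 × 0.90) = 257.5, so 258. Adding the percentages instead, 226 / 0.875 = 258.3, or 129 per arm.
- Drop-out allowance alone: 226 / 0.975 = 231.8, so 232.

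The stated 258 therefore reproduces only if the metastasised patients are outside the 226. The Background agrees: the 58% and 67% come from a cohort of patients who underwent distal pancreatectomy.

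**2. The two analysis sets.**
- Randomization rule: 258 × 0.975 = 251.6, about 252 (126 per arm).
- Sample-size basis: 258 × 0.975 × 0.90 = 226.4, about 226.
- Gap: about 25 patients.

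**3. Unresected patients excluded from R0.** 113 per arm and 80.2% power, as planned.

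**4. Unresected patients counted as not R0 (assumed, 10% in each arm).**
- Planned rates: 0.9 × 58% = 52.2% and 0.9 × 67% = 60.3%, a difference of 8.1 points.
- Standard error with 126 per arm: √[(0.522×0.478 + 0.603×0.397)/126] = 0.0623.
- Power: Φ[(0.081 + 0.07)/0.0623 − 1.645] = 78.2%.
- For 80% power: 133 per arm, 266 operated; 266/0.975 = 272.8, so 273 randomised (274 for equal arms).

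**5. Dilution under the same coding.**
- Suppose R0 among resected patients is truly 51% with MIDP and 58% with ODP. The diluted rates are 45.9% and 52.2%, a deficit of 6.3 points.
- Chance of declaring non-inferiority: Φ[(−0.063 + 0.07)/0.0629 − 1.645] = 6.3%. It is 5.6% to 7.0% if the metastasised share is 5% to 15%.
- A 7-point margin among all operated patients corresponds to 0.07/0.9 = 7.8 points among resected patients.
- If the hypothesis is set in all operated patients instead (45.2% against 52.2%, exactly −7 points), the chance is Φ(−1.645) = 5.0%.

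**6. Unequal shares (illustration only).** Take the same true deficit. With 8% metastasised in MIDP and 12% in ODP, the rates are 0.92×51% = 46.9% and 0.88×58% = 51.0%; the apparent deficit is 4.1 points and the chance about 12%. With the shares reversed, the chance is about 3%.

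**The case against.** The strongest reply is that the sections can be read together. The intention-to-treat sentence is a trial-wide rule that does not mention R0, and the Conversion section uses the term to mean analysis in the allocated arm. The Blinding section plans a sensitivity analysis of functional recovery without metastasised patients, so they evidently belong to that outcome's main analysis. On this reading they stay in the trial for other outcomes, R0 is assessed where there is a specimen, 258 was sized for that, and completeness refers to assessable patients. The reading is possible, so the sections are not beyond reconciliation. But no section states it, and the Randomization rule as worded has no exception.

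A second reply is that analysis sets belong in the analysis plan, which is promised before database lock. That would answer mere silence. It does not answer a stated rule that conflicts with the stated sample-size basis.

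A third reply stands in full: no section counts unresected patients as not R0, so the 78.2% and 6.3% depend on an assumed coding.

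A fourth also stands. A resected-only set conditions on an event after randomisation. Nor does it exactly restore the planning population: the cohort had PDAC, whereas the trial enrols suspected PDAC without mandatory pathological proof.

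A reader might also infer that the choice will be made after the data are seen. The documents do not show this: the analysis plan precedes database lock, and the pathologists and the adjudication committee are blinded.

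**Conclusion.** The point holds as an inconsistency in the primary analysis set. The Randomization rule implies about 252 patients analysed, the sample-size basis about 226, and the roughly 25 between them have no R0 status. That metastasised patients lie outside the 226 is inferred from the arithmetic and the source of the planning rates; the protocol does not say so outright.

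The size is modest. Exclusion keeps 80.2% power. Counting them as not R0 costs about 2 points of power and dilutes a true 7-point deficit among resected patients to 6.3 points, assuming 10% in each arm.

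Two stronger readings are not supported. The sample size is not miscalculated: 226 and 258 both reproduce. Nor does the test exceed its 5% level: the 6.3% is dilution relative to an effect defined in resected patients, and the level is 5.0% for an effect defined in all operated patients. This is a should-fix point.

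**What to change.** Before outcome data are seen, state one primary R0 denominator and the R0 status of unresected patients, consistently in Randomization, Sample size calculation and Statistical analysis. Either choice is workable:

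- **Resected patients.** 226 and 258 stand. The Randomization section needs an explicit exception for R0, with unresected patients kept for the other outcomes.
- **All operated patients, unresected counted as not R0.** Restate the planned rates as 52.2% (ODP) and 60.3% (MIDP) and power as about 78%.

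In either case, pre-specify the other set as a sensitivity analysis. Report unresected patients by arm, because a resected-only set conditions on a post-randomisation event and an imbalance could move the result either way. Limit the completeness statement to patients with a specimen.

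The cost is wording and one additional analysis, with no new data. Under the second choice, stated power falls by about 2 points; restoring 80% would need 273 or 274 randomised, 15 or 16 more than 258.
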